## Results

This randomized controlled trial is funded by the Ministry of Science and Technology Council, Taiwan, from August 2023 to July 2026. The trial was registered in August 2024 (ClinicalTrials.gov NCT06520592). Participant recruitment is scheduled to commence in April 2025, with follow-up assessments planned at 1 month (T1), 3 months (T2), and 6 months (T3) post intervention.

We plan to enroll 40 participants by September 2025, representing 50% of the targeted sample size of 80. Preliminary analyses of baseline adherence and usability data are underway. The trial remains on schedule, with the final data collection anticipated in December 2025 and results expected to be published by Fall 2026.

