**Results:**

This study is funded by the Ministry of Science and Technology, Taiwan (August 2023 to July 2026) and was registered in August 2024 (ClinicalTrials.gov NCT06520592). Participant recruitment is scheduled to begin in April 2025, and by September 2025, we expect to have enrolled 40 participants (50% of the target sample of 80). Preliminary analyses of CPAP adherence at 1 month and usability data are currently underway. Final data collection is anticipated to be completed by December 2025, with results expected to be published by Fall 2026.

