## Methods

### Study Design

This parallel group randomized controlled trial is designed to evaluate the effectiveness of AR-guided CPAP therapy on patient adherence among individuals diagnosed with OSA. Participants will be randomly assigned to either the experimental group (AR-guided therapy) or the control group (standard care) by the blocking sample method. Aside from the AR component, both groups will receive identical standard care. An assistant researcher ([name]) generated the random allocation sequence, case managers enrolled participants with OSA, and an assistant researcher ([name]) assigned participants to interventions. In this study, we will blind assessors and investigators. The study will follow participants over 6 months, with data collection points at baseline (T0), and follow-ups at 1 month (T1), 3 months (T2), and 6 months (T3) post intervention.

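### The stated calendar is impossible: with 40 of 80 enrolled by September 2025 and a 6-month final visit, data collection cannot end in December 2025

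*Protocol article*

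**What the plan says.** The calendar appears in the Abstract (Results) and again in the Results section, with the same dates.

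- Start and visits (Results): "Participant recruitment is scheduled to commence in April 2025, with follow-up assessments planned at 1 month (T1), 3 months (T2), and 6 months (T3) post" (that is, timed from the intervention).
- Enrolment milestone (Results): "We plan to enroll 40 participants by September 2025, representing 50% of the targeted sample size of 80". The Abstract gives the same milestone.
- Close (Results): "The trial remains on schedule, with the final data collection anticipated in December 2025 and results expected to be published by Fall 2026". The Abstract agrees: "Final data collection is anticipated to be completed by December 2025".
- Follow-up (Methods, Study Design): "The study will follow participants over 6 months", with T3 as the last visit.
- Funding (Results): "from August 2023 to July 2026".

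Methods, Primary Outcomes, has the CPAP device data collected at T1, T2 and T3. Methods, Data Analysis, compares the groups at each visit, T3 included, in a mixed-effects repeated-measures model. Methods, Sample Size, sets the target at 80 (40 per group) with a 20% dropout allowance.

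The article nowhere describes December 2025 as an interim cut, restricts T3 to a subset, or lowers the target of 80.

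**The concern.** Three months separate the point at which half the sample is enrolled and the point at which data collection ends, while each participant needs six months of follow-up. The second half of the sample cannot fit into that gap, and neither can those of the first half who enrol after June.

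The closing date decides for whom the 6-month adherence outcome exists. If data collection stopped as written, T3 would be missing for at least half the participants because of the calendar alone, before any dropout. Long-term adherence is what the trial sets out to improve, and T3 is its only observation beyond 3 months.

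**Working it through.** **Inputs.** Recruitment start April 2025; 40 of 80 enrolled by September 2025; final data collection December 2025; funding to July 2026 (all Results). T3 at 6 months and T2 at 3 months (Study Design). 20% dropout (Sample Size).

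**1. The plan's own figure.** 40/80 = 0.50, so the 50% milestone reproduces.

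**2. Latest enrolment that allows T3.** Close minus 6 months: 31 December 2025 − 6 months = 30 June 2025. T3 counts from the intervention, so any delay between enrolment and intervention moves this date earlier.

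**3. Lower bound on the loss, with no pace assumption.** Participants not yet enrolled at the milestone number 80 − 40 = 40. Even one enrolled on 1 September 2025 reaches T3 on 1 March 2026, after the close. So at least 40/80 = 50% cannot have T3. The bound is reached only if all of the first 40 enter by 30 June; those enrolled in July to September have T3 in January to March 2026 and miss it too.

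**4. Comparison with the dropout allowance.** 80 × (1 − 0.20) = 64 completers planned. The most that could have T3 by the close is 40.

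**5. Likely size under even accrual (an assumption).** Number with T3 = 40 × (days from start to the enrolment cut-off) / (days from start to milestone). Taking 1 April, 30 September and 31 December: 40 × 90/182 = 19.8, about 20 of 80, so about 60 (75%) without T3. The article gives months only, so each date was varied over the first and last day of its month. The last two columns continue the same pace to the 80th participant and add 6 months.

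| Start | Milestone | With T3, close 1 Dec | With T3, close 31 Dec | 80th enrolled | Last T3 |
|---|---|---|---|---|---|
| 1 Apr | 1 Sep | 15.9 | 23.5 | 1 Feb 2026 | 1 Aug 2026 |
| 1 Apr | 30 Sep | 13.4 | 19.8 | 31 Mar 2026 | late Sep 2026 |
| 30 Apr | 1 Sep | 10.3 | 19.7 | 3 Jan 2026 | 3 Jul 2026 |
| 30 Apr | 30 Sep | 8.4 | 15.9 | 2 Mar 2026 | 2 Sep 2026 |

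So 8 to 24 participants would have T3, and 56 to 72 (71% to 90%) would not.

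**6. Earlier visits.** 31 December − 3 months = 30 September: anyone enrolled after that date also misses T2. At 40/6 = 6.67 per month from 1 April, about 40 participants would have T2 and 6.67 × 8 = 53 (enrolled by the end of November) would have T1.

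**7. Funding.** T3 by the end of July 2026 requires enrolment by the end of January 2026. At 6.67 per month, 6.67 × 10 = 67 participants would be enrolled by then. Reaching 80 would need the last 40 in October to January, 40/4 = 10 per month.

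**The case against.** The best defence is that December 2025 is simply a wrong date. It is only anticipated, and publication in Fall 2026 and funding to July 2026 leave room for a later close. No design element (target, follow-up length or outcome) is itself wrong. Objective adherence is monitored daily through a cloud system, so those data could be retrieved after December. The harm is therefore conditional on the date being followed. That much stands. It does not remove the contradiction, because both places that give the calendar call December 2025 the final data collection, and the Results section adds that the trial is on schedule. Cloud retrieval after December would itself depart from the stated close, and it would not supply the self-reported adherence, adverse-effect or usability data. Faster enrolment is no answer either: full T3 by December would need all 80 enrolled by the end of June, against the article's own milestone.

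A reader might infer three stronger points that the article does not support.

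- **A specific power loss.** If 32 per group have 85% power, the detectable standardised difference in a t-test is 0.76, and 10 to 12 per group would then have 36% to 43% power. This is illustrative at most. The 0.76 is back-solved; the article gives an effect size of 0.32 of unstated type. The planned analysis is a repeated-measures model over all visits and not a T3-only t-test. And the 32 is net of dropout while the 10 to 12 is not.
- **A void sample-size statement.** The target of 80 is untouched by this point once the closing date is corrected. What fails is the assumption of 64 completers at T3 under the stated close.
- **A certain funding overrun.** The article gives no pace for the second 40. Continuing the implied pace puts the last T3 between early July and late September 2026, and the early end lies within the funding period. This is a risk to check and not a contradiction.

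**Conclusion.** The point holds: the September 2025 milestone, the 6-month follow-up and the December 2025 close are mutually incompatible. At least 40 of 80 participants (50%) cannot have T3 by the stated close. This bound takes the milestone at face value and needs no further assumption. Under even accrual the number with T3 is about 20 (8 to 24 over the readings of the month names). Either figure is far below the 64 completers that the dropout allowance implies.

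The consequence is limited to what would be lost if the date were followed. The mixed model would still use the T1 and T2 data, but it cannot supply 6-month observations that were never collected, and late enrolees would lack T2 as well. The closing date is wrong as written and has to be corrected before it governs data collection.

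**What to change.** 1. In the Abstract and the Results section, replace the December 2025 date by a rule: data collection closes when the last of the 80 randomised participants reaches T3. Give the expected date with the accrual assumption behind it.
2. Remove the statement that the trial is on schedule.
3. Move the analysis and publication dates to follow the new close. With a last T3 in late September 2026, publication by Fall 2026 would leave almost no time for analysis.
4. Check the new close against the July 2026 funding end. If that end is fixed, state the last enrolment date that permits T3 (about the end of January 2026) and the N it yields: about 67 at 6.67 per month, or 80 only if enrolment after September runs at about 10 per month.

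The cost is revised dates and a later close and publication, and possibly a funding extension. Target, visits, outcomes and model stay as they are, unless a fixed funding end forces a smaller N.

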## Discussion

### Summary of Principal Findings

This prospective observational study is anticipated to yield valuable insights into the effectiveness of AR-guided CPAP therapy in improving adherence among patients with OSA. Specifically, the study focuses on facilitating the selection of appropriately fitting mask sizes, providing hands-on training on proper mask use, and offering troubleshooting support. If the hypothesis is validated, AR technology could emerge as a powerful tool to enhance patient engagement and address machine interface barriers to CPAP adherence, such as discomfort, leakage, and lack of motivation. The study’s results could have broader implications for the management of OSA and other chronic conditions that require long-term adherence to therapeutic regimens.

### Comparison to Prior Work

Previous studies have explored telemonitoring and cognitive behavioral therapy to improve CPAP adherence, but research integrating AR technology into CPAP management remains limited. By addressing this gap, our study contributes to the growing evidence on technology-assisted interventions for chronic disease management.

### Strengths and Limitations

A strength of this study is the comprehensive assessment of adherence, incorporating both objective adherence tracking and subjective self-reported adherence evaluation. This multidimensional approach enhances the study’s ability to identify barriers to CPAP adherence and potential intervention strategies to improve long-term compliance. Additionally, this study has a randomized controlled design, which enhances the validity and reliability of the findings. Another strength is that the integration of AR technology allows for real-time patient education and support, which has the potential to improve CPAP adherence through enhanced engagement and interactive learning.

However, some potential limitations should be considered. First, generalizability may be limited due to the specific population studied. Since the study is conducted in a single region with a particular demographic profile, findings may not be fully applicable to other populations with different cultural, socioeconomic, or health care structures. Second, the novelty of AR technology may present implementation challenges, particularly among older adults or patients with low technology literacy, potentially limiting the accessibility and effectiveness of the intervention. Lastly, variations in AR device compatibility across different CPAP models could pose practical barriers to widespread adoption.

### Future Directions

To address these limitations, future research should explore multicenter studies across diverse populations and investigate strategies to enhance AR accessibility for less tech-savvy users, such as simplified interfaces or additional training modules.

### Dissemination Plan

The results of this study will be disseminated through peer-reviewed publications, conference presentations, and clinical workshops. Additionally, findings may inform the development of AR-based educational modules for sleep medicine practitioners.

### Conclusions

This study is expected to provide valuable insights into the role of AR-guided CPAP therapy in improving adherence among patients with OSA. By integrating real-time interactive guidance, the intervention aims to enhance patient engagement, improve mask fitting, and address adherence barriers such as discomfort and lack of motivation. While findings from this study may support the use of technology-driven interventions in CPAP management, further research will be needed to explore long-term effectiveness, broader applicability across different populations, and strategies to optimize accessibility for patients with lower technology literacy. If validated, this study could inform future clinical practice by integrating AR-based patient education and support tools into standard CPAP care, potentially improving adherence and long-term treatment outcomes for patients with OSA.

## Appendix

Multimedia Appendix 1 Subjective Questionnaire: CPAP Adherence and Comfort Assessment.

Multimedia Appendix 2 System Usability Scale.

## Abbreviations

AR: augmented reality
CPAP: continuous positive airway pressure
OSA: obstructive sleep apnea
